**Patient-reported outcomes**									
	PHQ-9	X		X		X		X	
	SDS	X		X		X		X	
	WPAI	X		X		X		X	
	PDQ-D	X		X		X		X	
	EQ-5D-5L	X		X		X		X	

^a^The starting date of antidepressant treatment (ie, the first day of administration) is defined as Day 1.

^b^Informed consent is required before any clinical research procedures are performed.

^c^Conducted only in patients at preselected research sites (approximately 100 patients).

For the secondary analyses, changes from baseline at each assessment time point will be calculated for SDS, WPAI, UPSA-B, PDQ-D and EQ-5D-5L scores. The association between cognitive function and depressive symptoms will be assessed using the DSST and MADRS categories at each visit. Correlations between DSST scores and SDS, WPAI, and EQ-5D-5L scores (individually) will be calculated using Pearson's and Spearman's correlation coefﬁcients. SDS, WPAI, UPSA-B, and EQ-5D-5L scores at each assessment point will be compared using analysis of variance models, according to the DSST category at baseline. Similar analysis will be performed for PDQ-D as the primary measure of cognitive function (scores will be allocated to one of four categories; the cutoffs being based on quartiles).

As an exploratory investigation, univariate and multivariate logistic regression analyses will be conducted to determine whether the presence of cognitive dysfunction is a predictor of response, remission, and relapse of depressive symptoms. Patients with a ≥50% reduction from baseline in MADRS score at month 1 are categorized as treatment responders. Patients with a MADRS score of ≤10 at month 2 and/or 6 are categorized as having achieved symptomatic remission. Patients who achieved remission at an earlier visit and have a MADRS score ≥22 at month 6 are categorized as having relapsed in terms of depressive symptoms. Factors for the logistic regression analyses (eg, DSST score, PDQ-D score, MADRS score, age, gender, educational level, and employment status), will be selected for their clinical relevance based on the literature [9]. Exploratory analyses will also evaluate correlations between scores on the UPSA-B, DSST, WPAI (if the sample size allows), EQ-5D-5L, and MADRS scales. Statistical tests will be two-sided at the 5% signiﬁcance level, if not otherwise specified.

In subgroup analyses, all data will be summarized according to the MADRS category at baseline, and according to age group.

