A target sample size of 500 patients was estimated in order to ensure acceptable precision of the mean change from baseline in DSST scores at months 2 and 6. Based on two previous studies which investigated the effect of vortioxetine on cognitive function in MDD [30,31], assuming a standard deviation of 8.1 and a withdrawal rate of 25% at month 6, 500 enrolled patients will ensure a value of 0.82 for the half-width of the two-sided 95% confidence interval for the change in DSST score from baseline to month 6.

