## Results

The PERFORM-J study began in September 2016. Patient enrollment was completed on June 30, 2017, with 523 patients having been enrolled from 48 sites, with the UPSA-B assessment having been conducted on 141 patients. As of October 2017, 279 patients have completed the study.

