## Discussion

PERFORM-J is the first study conducted in Japan to prospectively evaluate longitudinal changes in cognitive function, depressive symptoms, and other functional outcomes in patients with MDD following the start of antidepressant therapy. The information obtained will shape our understanding of how antidepressants affect cognition in Japanese patients. Importantly, the study includes both physician- and patient-rated tests of cognitive function, administered to a large group of patients treated in accordance with current clinical practice in Japan. A noninterventional design was chosen to avoid interference with standard practice.

The prospective design and the number of study sites should facilitate collection of data that is sufficient to represent the MDD population in Japan. The 6-month study period should be long enough to detect the effects of antidepressants on depressive symptoms. The study period will also allow detection of meaningful changes in functional outcomes and utilization of healthcare resources over time. In fact, the study design is similar to that of PROACT (Prospective Research Observation to Assess Cognition in Treated MDD patients), currently ongoing in China, and PERFORM-K in South Korea [32].

Currently, cognitive function does not appear to be a major concern among Japanese psychiatrists who treat mood disorders. Therefore, the current study should provide valuable information to facilitate improvements in functional outcomes in patients with MDD.

A major limitation of this study relates to the uncontrolled and observational study design, which does not allow evaluation of cause and effect relationships. Additionally, patients can take concomitant medication, potential effects of which on cognition cannot be excluded.

In conclusion, we have described the protocol of a prospective, multi-center study of the longitudinal relationship between cognitive dysfunction, severity of depressive (mood) symptoms, and higher-level functional outcomes in Japanese patients with MDD. Results from PERFORM-J should provide valuable information regarding the potential of antidepressant monotherapy to improve symptoms and social functioning in such patients.

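### The half-width of 0.82 for the DSST change at month 6 assumes independent patients, although they come from 48 sites; it is guaranteed only if the intra-site correlation is zero

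*Protocol article*

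**What the plan says.** The sample size is justified by precision alone. In the Protocol article, at the end of Methods, Statistical Analysis: "A target sample size of 500 patients was estimated in order to ensure acceptable precision of the mean change from baseline in DSST scores". The time points meant are month 2 and month 6. The inputs are given as "assuming a standard deviation of 8.1 and a withdrawal rate of 25% at month 6", and the result is that "500 enrolled patients will ensure a value of 0.82 for the half-width of the two-sided 95% confidence interval" for the change to month 6. No correlation within sites and no design effect is mentioned.

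The Results section reports "523 patients having been enrolled from 48 sites". The Discussion expects the prospective design and the number of sites to help yield data "sufficient to represent the MDD population in Japan".

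The primary analyses in the same Methods section are changes from baseline in DSST and MADRS. The article does not say how site enters their standard errors.

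**The concern.** A mean change estimated from patients grouped in 48 sites has the standard error of a simple random sample only if patients at one site are no more alike in their change than patients at different sites. If they are more alike, part of the variance lies between sites, and the standard error of the mean is larger than SD/√n.

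The article gives reasons why change could differ between sites. The antidepressant is chosen on the physician's judgement, and additions and dose modifications are allowed under routine practice (Methods, Patients). The DSST and MADRS are listed among the physician-rated assessments (Table 1). Because the Discussion looks beyond these sites to patients with MDD in Japan, between-site variation belongs in the uncertainty of the mean.

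At stake is the one quantitative design property that the article states, and the width of the confidence intervals around the primary mean changes.

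**Working it through.** **Inputs from the Protocol article**
- Enrolled: 500; SD of DSST change: 8.1; withdrawal by month 6: 25% (Methods, Statistical Analysis).
- Evaluable at month 6: 500 × 0.75 = 375.
- Sites: 48; actual enrolment: 523 (Results).

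**Assumptions, because the document gives no figure**
- ICC of DSST change: 0.01, 0.02, 0.05 and, as a high value, 0.10.
- Coefficient of variation (CV) of site size: 0 (equal sites) or 0.6.

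**Step 1. Reproduce the plan's figure.** Half-width = 1.96 × 8.1/√375 = 15.876/19.365 = 0.820. In reverse, (1.96 × 8.1/0.82)² ≈ 374.8 evaluable patients, or 374.8/0.75 ≈ 499.8 enrolled. The stated inputs use up the whole figure, so it contains no design effect.

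**Step 2. Allow for sites.** Mean evaluable patients per site: m = 375/48 = 7.81. The design effect for a mean is DE = 1 + [(1 + CV²) × m − 1] × ICC.
- Equal sites: DE = 1 + 6.81 × ICC.
- CV 0.6: (1.36 × 7.81) − 1 = 9.63, so DE = 1 + 9.63 × ICC.

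Half-width = 0.820 × √DE. True coverage of a nominal 95% interval that ignores site = 2Φ(1.96/√DE) − 1.

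| ICC (assumed) | DE, equal sites | Half-width | Coverage if site ignored | DE, CV 0.6 | Half-width |
|---|---|---|---|---|---|
| 0 | 1.000 | 0.82 | 95% | 1.000 | 0.82 |
| 0.01 | 1.068 | 0.85 | 94.2% | 1.096 | 0.86 |
| 0.02 | 1.136 | 0.87 | 93.4% | 1.193 | 0.90 |
| 0.05 | 1.341 | 0.95 | 90.9% | 1.481 | 1.00 |
| 0.10 | 1.681 | 1.06 | 86.9% | 1.963 | 1.15 |

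At ICC 0.05 with equal sites, the 375 evaluable patients carry the information of 375/1.341 ≈ 280 independent ones.

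**Step 3. Does the larger enrolment make up for it?** With 523 enrolled and 25% withdrawal, 523 × 0.75 = 392 are evaluable, or 8.17 per site. The half-width is 1.96 × 8.1/√392.25 = 0.80 at ICC 0. With equal sites it is 0.83 at ICC 0.01 and 0.93 at ICC 0.05. The extra patients offset a design effect of 392.25/375 = 1.046, that is, an ICC of 0.046/7.17 ≈ 0.006. Above that, the half-width exceeds 0.82 again.

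**The case against.** **The figure is not wrong.** It follows exactly from its stated inputs and is a conventional planning calculation. This stands: the dispute is with the unstated assumption of independence and the unconditional wording.

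**The ICC may be small.** The half-width concerns within-patient change, so stable site differences in level cancel. The DSST is timed and scored by counting correct answers, which leaves less room for rater effects than the MADRS. At ICC 0.01 with equal sites the half-width grows by only 0.03 points on a 0–133 scale. This stands as a limit on size. It does not remove the point, because subtracting baseline does not remove site differences in change, and the document cannot settle the ICC.

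**Little hangs on 0.82.** The plan asks for acceptable precision without naming a threshold, no test depends on the figure, and enrolment is complete. This also stands, and it is why no more patients are called for.

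**A stronger reading that the document does not support.** A reader might infer that all the planned analyses ignore site, so that their intervals are too narrow and their p-values too optimistic. The article is silent on site, gives its logistic factors only as examples, and may leave the variance method to a full protocol or analysis plan that is not shown. Moreover, the design effect for a mean does not carry over to the secondary comparisons, in which scores "will be compared using analysis of variance models, according to the DSST category at baseline", or to the correlations and logistic models. Their predictors vary between patients within a site, so ignoring site there could make standard errors too small, nearly unchanged or too large.

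**Conclusion.** The point holds for the precision statement and, by the same reasoning, for the confidence intervals of the primary mean changes. A later analysis plan cannot change what 0.82 assumes: if that plan does allow for site, 0.82 does not describe the interval to be reported unless the between-site variance of change is zero.

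Over assumed ICCs of 0.01 to 0.05, the half-width is about 3% to 16% above the stated 0.82 with equal sites (√1.068 = 1.03, √1.341 = 1.16), and up to 22% above it with a site-size CV of 0.6 (√1.481 = 1.22). These sizes rest on the assumed ICC and site-size spread, and on the plan's own SD and withdrawal rate. The undercoverage applies only if the analysis ignores site and the ICC is positive. For MADRS change the same reasoning applies, but the document gives no SD, so no half-width is computed. This is a modest correction to a descriptive cohort study and does not call its design into question.

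**What to change.** 1. Compute the confidence intervals for the primary mean changes in DSST and MADRS with site-clustered robust standard errors. These leave the estimated mean unchanged. A site random intercept would re-weight sites of unequal size and could move the mean as well as the interval.
2. Restate the precision along these lines: *about 0.82 assuming independent patients; about 0.85 to 1.00 for an intra-site correlation of 0.01 to 0.05*. The range runs from equal sites at ICC 0.01 to a site-size CV of 0.6 at ICC 0.05. Label the ICC and the CV as assumptions.
3. State how site is handled in the secondary and exploratory models, without presuming which way it will move the results.

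The cost is one variance option, one restated sentence and a slightly wider interval. The figures above use 1.96. If the clustered interval uses a t quantile on 47 degrees of freedom (2.01), they rise by a further 2.6% or so, for example from 0.82 to 0.84 and from 0.95 to 0.97. No more patients are needed.

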## Results

The PERFORM-J study began in September 2016. Patient enrollment was completed on June 30, 2017, with 523 patients having been enrolled from 48 sites, with the UPSA-B assessment having been conducted on 141 patients. As of October 2017, 279 patients have completed the study.

## Discussion

PERFORM-J is the first study conducted in Japan to prospectively evaluate longitudinal changes in cognitive function, depressive symptoms, and other functional outcomes in patients with MDD following the start of antidepressant therapy. The information obtained will shape our understanding of how antidepressants affect cognition in Japanese patients. Importantly, the study includes both physician- and patient-rated tests of cognitive function, administered to a large group of patients treated in accordance with current clinical practice in Japan. A noninterventional design was chosen to avoid interference with standard practice.

The prospective design and the number of study sites should facilitate collection of data that is sufficient to represent the MDD population in Japan. The 6-month study period should be long enough to detect the effects of antidepressants on depressive symptoms. The study period will also allow detection of meaningful changes in functional outcomes and utilization of healthcare resources over time. In fact, the study design is similar to that of PROACT (Prospective Research Observation to Assess Cognition in Treated MDD patients), currently ongoing in China, and PERFORM-K in South Korea [32].

Currently, cognitive function does not appear to be a major concern among Japanese psychiatrists who treat mood disorders. Therefore, the current study should provide valuable information to facilitate improvements in functional outcomes in patients with MDD.

A major limitation of this study relates to the uncontrolled and observational study design, which does not allow evaluation of cause and effect relationships. Additionally, patients can take concomitant medication, potential effects of which on cognition cannot be excluded.

In conclusion, we have described the protocol of a prospective, multi-center study of the longitudinal relationship between cognitive dysfunction, severity of depressive (mood) symptoms, and higher-level functional outcomes in Japanese patients with MDD. Results from PERFORM-J should provide valuable information regarding the potential of antidepressant monotherapy to improve symptoms and social functioning in such patients.

## Abbreviations

CGI-S: Clinical Global Impression - Severity
DSM-IV-TR: Diagnostic and Statistical Manual of Mental Disorders, 4th Edition, Text Revision
DSST: Digit Symbol Substitution Test
EQ-5D-5L: EuroQoL 5-Dimensions, 5-levels
MADRS: Montgomery-Asberg Depression Rating Scale
MDD: Major Depressive Disorder
MINI: Mini International Neuropsychiatric Interview
PDQ-5: Perceived Deficit Questionnaire-5 item
PDQ-D: Perceived Deficits Questionnaire-Depression
PHQ-9: Patient Health Questionnaire-9 item
SDS: Sheehan Disability Scale
UPSA-B: University of California, San Diego Performance-based Skills Assessment-Brief
VAS: Visual Analog Scale
WPAI: Work Productivity and Activity Impairment questionnaire
